## SCHEDULE OF ASSESSMENTS

| Study Procedure                                                                              | Visit 1 | Visit2 | Visit3 | Visit 4 | Visit 5 | Visit 6 | Visit 7 |
|----------------------------------------------------------------------------------------------|---------|--------|--------|---------|---------|---------|---------|
| Obtain Informed Consent from patient or relative incapacity form                             | √       |        |        |         |         |         |         |
| Review Inclusion/Exclusion Criteria                                                          | √       |        |        |         |         |         |         |
| Recruit patient if appropriate and undertake study over 3days                                | √       |        |        |         |         |         |         |
| Day 1- monitor secretions, undertake Qualitative Sputum Analysis and respiratory physiology  |         | √      | √      |         |         |         |         |
| Day 2 - monitor secretions, undertake Qualitative Sputum Analysis and respiratory physiology |         |        |        | √       | √       |         |         |
| Day 3 - monitor secretions, undertake Qualitative Sputum Analysis and respiratory physiology |         |        |        |         |         | √       | √       |

## **1. INTRODUCTION**

### **1.1 Background**

Critically unwell patients in Intensive Care have a decreased ability to effectively clear secretions. This is often multifactorial and can include respiratory muscle weakness, impaired cough and low conscious level. In addition the amount of secretions can be higher than normal due to intercurrent infection or aspiration. High secretion load is a major risk factor in the failure of tracheal extubation failure and requirement for reintubation. Extubation failure is a predictor of poor outcome independent of the severity of the underlying illness. Nebulisation of isotonic saline can be employed to manage secretions by reducing the secretion viscosity and facilitating clearance of respiratory sections during tracheal suction.

We are testing the hypothesis that regular (or continuous) small doses of nebulised normal saline will benefit lung physiology in mechanically ventilated patients (with a heat and moisture exchanger filter in the circuit). This practice of additional nebulisation is commonplace in ICUs when secretions management is problematic.

If totally dry gases were inspired and fully saturated gases exhaled the total water loss from ventilation at rest would be about 300 ml/day in the average adult. Bypassing the nose with an endotracheal tube and not humidifying gases causes maximal losses. This is mitigated by using a heat and moisture exchange filter (HME) in the circuit. The standard HME is 80 % efficient then the water loss from the airway will be around 60ml/day. Patients with underlying lung issues or difficult to manage secretions may benefit from optimised airway hydration and improved lung physiology.

Standard jet nebulisers have been the mainstay of respiratory section management therapy for in critical care since the early 1990's. A more recent development has been the vibrating mesh nebuliser. There is evidence of improved humidification and reduced water particle size and theoretically better transfer to the distal airways.

### **1.2 Rationale**

The vibrating mesh nebuliser (Aerogen technology) may be superior to standard nebuliser technology.

### **1.3 Study hypothesis**

Improved secretion management with reduced tenacity of respiratory sections and potentially improved lung physiology secondary to improved humidification or reduced size of nebulised particles?

## **2. STUDY OBJECTIVES**

### **Primary Endpoint**

- Pourability of respiratory secretions (As assessed by the Qualitative Sputum Assessment Tool)

(The QSA score will assess quantity, quality/stickiness/density and colour/appearance of secretions and is described and validated in the literature)

### **Secondary endpoints**

- Volume of secretions (increased or decreased may be beneficial)
- Work of breathing
- Airway resistance
- Number of additional nebulised doses of saline or other drugs administered during the study period
- Ease of sampling, in opinion of treating nurse
- Frequency of requiring changing the HME filter
- Length of time on ventilator
- Length of stay in ICU
- ICU Mortality

## **3. STUDY DESIGN**

### **3.1 Study Population**

A total of 60 patients will be recruited to the study. Each patient will be randomised to receive:

Continuous nebulisation of 0.9% normal saline using the Aerogen Solo Nebuliser (50mls/24h via a syringe feed set) OR

Intermittent nebulisation of 0.9% normal saline using the Aerogen Solo Nebuliser (5mls, 6 hourly) OR

Intermittent standard nebulisation of 0.9% normal saline using the Intersurgical Cirrus 2 self-sealing Jet Nebuliser (5 mls, 6 hourly)

### **3.2 Inclusion criteria**

- Patient aged 18-80 years at time of recruitment to study
- Ventilated via an endotracheal tube or tracheostomy with an HME filter in the circuit

- Secretion load defined as patient requiring suctioning at least 2 times in the 6 hours prior to recruitment
- Sputum viscosity with grades 1 to 3 pourability in the Qualitative Sputum Assessment tool
- Not yet received saline nebulisation in the 6 hours prior to recruitment
- Likely to be ventilated via an endotracheal tube or tracheostomy for at least 3 days in the opinion of the treating clinician

### **3.3 Exclusion criteria**

- Pregnancy
- Pulmonary embolus
- Heart Failure (NYHA Grade III/IV)
- Clinical evidence of frank pulmonary oedema
- Cardiovascular instability (systolic BP  $\leq 75$  or heart rate  $\geq 140$ )

### **3.4 Identification of participants and consent**

Patients with acute respiratory failure will be screened in the Intensive Care Units of the Queen Elizabeth university hospital.

#### **i) Patient with capacity:**

- The patient will be provided with a written 'Patient Information Sheet'.
- A member of the research team with relevant GCP training will provide verbal information and answer any questions.
- If the patient chooses to be enrolled in the study, they will sign a 'Patient Consent Form'.
- The patient may withdraw consent at any stage (as explicitly stated in the 'Patient Information Sheet').

#### **ii) Patient without capacity, when a legal representative is immediately available:**

- When a patient does not have capacity the research team will attempt to identify a legal representative [in accordance with the 'Adults with Incapacity (Scotland) Act 2000' (Scotland)]
- The legal representative will be provided with a written 'Legal Representative Information Sheet'.
- A member of the research team with relevant GCP training will provide verbal information and answer any questions.
- The legal representative will be asked to use their knowledge of the patient's beliefs to advise the research team as to whether they feel the patient would choose to enrol in the study.
- When the legal representative feels the patient would have chosen to enrol in the study, they will be asked to sign a consent form on behalf of the incapacitated adult.

- The legal representative may withdraw the patient at any stage (as explicitly stated in the 'Legal Representative Information Sheet').
- In the event that the patient regains capacity, the research team will speak to the patient at the earliest opportunity and ask the patient to provide retrospective consent; if the patient chooses to continue to be part of the study they will sign a 'Consent Form to continue'; if the patient gives consent to continue, they are free to withdraw their consent at any time; if the patient does not wish to consent, they will be withdrawn from the study.
- In the event that the patient never regains capacity or dies then he/she will remain in the study and their data will be included in the final analysis.

iii) Patient without capacity, when a Legal Representative is not immediately available, and no appropriate person is identified:

- When a patient does not have capacity and the research team are unable to identify or contact an appropriate legal representative, (Welfare Attorney, Welfare Guardian or Nearest Relative) the patient should not be enrolled into the study.

### **3.5 Withdrawal of subjects**

Patients will be withdrawn if they cannot tolerate nebulisation via either method or if there is concern by the treating clinician at any point during the study.

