### **4.2 Study Outcome Measures**

#### **4.2.1 Primary Outcome Measure**

- Median change of all viscosity (pourability) of respiratory secretions as assessed by a dedicated team or physiotherapists using the Qualitative Sputum Assessment Tool Scores taken at 10:00 and 16:00 while the patient is recruited to the study

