## **5. ASSESSMENT OF SAFETY**

Throughout the duration of the study period the recruited patients will be closely monitored by a Intensive Care Nurses and critical care physicians. They will have continuous monitoring of their oxygen saturations (SpO2), heart rate, with regular monitoring of blood pressure. As part of standard care patients will have regular monitoring of their ventilator parameters including the tidal volume being delivered and airway pressures.

The treating clinician can stop the nebulisation if at any point they have clinical concern and institute any rescue therapy deemed necessary.

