## **7.6 Sample size**

This is a pilot feasibility study and a total of 20 patients in each group is adequate to provide information to power a definitive study. The chosen samples sizes can be further justified as follows:

We will determine if the primary end point (viscosity even you are looking at the change in the score from baseline to final measurement, assuming the score is 1 to 4 in 0.5 increments at each time point, the distribution in values of change could range from -3 to +3 in 0.5 increments. This can therefore be treated as a continuous measurement. With 20 subjects we estimate an 80% power to detect a difference between any 2 groups of 0.503 per standard deviation (effect size=0.503) for the change in score. This assumes a significance level (p value) of 0.0167 to take into account that we would use 3 comparisons:

1. (Intermittent standard nebulisation vs. Continuous Aerogen nebulisation,
2. Intermittent standard nebulisation vs. Intermittent Aerogen nebulisation,
3. Continuous Aerogen nebulisation vs. Intermittent Aerogen nebulisation)

The statistically analysis and powering of this study were based on advice for [name] senior statistician the Robertson Centre, 24th July 2019.

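### Withdrawal for intolerance or clinician concern (3.5), read with 4.2.1, ends sputum grading after a treatment-related event and can bias the results

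*Protocol*

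**What the plan says.** Section 3.5, on withdrawal of subjects, reads: "Patients will be withdrawn if they cannot tolerate nebulisation via either method or if there is concern by the treating clinician". The rule applies throughout the study.

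Section 4.2.1 defines the primary outcome as "Median change of all viscosity (pourability) of respiratory secretions", using "Scores taken at 10:00 and 16:00 while the patient is recruited to the study".

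Section 5 deals with stopping treatment as a separate matter: "The treating clinician can stop the nebulisation if at any point they have clinical concern and institute any rescue therapy deemed necessary". It does not say whether sputum grading goes on afterwards.

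The only explicit retention rule is in section 3.4 (ii). A patient enrolled through a legal representative who never regains capacity or "dies then he/she will remain in the study and their data will be included in the final analysis". That rule does not mention patients withdrawn for intolerance or clinician concern.

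**The concern.** Intolerance and clinician concern arise after randomisation and may be consequences of the allocated method. If they end a patient's participation, and scores count only during participation, outcome data stop at an event that treatment can influence. The secondary outcomes that run beyond the treatment period (ventilator time, ICU stay, ICU mortality) may stop with them.

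The rate of such events could differ between arms, because the arms differ in device, schedule and volume. Section 3.1 gives 50 ml per 24 hours in the continuous arm and 5 ml every 6 hours, that is 4 × 5 = 20 ml per 24 hours, in the two intermittent arms. Section 6.1 anticipates bronchospasm, fluid in the circuit and chest tightness, each a plausible reason for intolerance or concern.

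Two things are at stake: the three-arm comparison, for which the synopsis plans a Kruskal-Wallis test and section 7.6 three pairwise contrasts; and the outcome distributions, which section 7.1 says will inform the power of a further study.

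**Working it through.** **Does the text end data collection?**

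- Section 5 already provides for stopping nebulisation. Section 3.5 uses a different term, withdrawal, applied to the subject.
- Section 3.4 (ii) uses the same verb, with the study named as what is left, for a patient who regains capacity and declines to continue.
- Section 4.2.1 ties the scores that count to the time on study.
- Nowhere does the protocol say that grading continues after nebulisation stops, or that ICU outcomes are still collected after a withdrawal under 3.5.

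**What is lost for a withdrawn patient?** Nothing says that scores before withdrawal are discarded. Under 4.2.1 such a patient contributes a median over fewer scores. Under section 7.6, which works with "change in the score from baseline to final measurement", the final measurement becomes the last one before withdrawal. If withdrawal comes before the first post-baseline grading, the patient contributes nothing.

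**How large could the effect be?** The protocol states no withdrawal rate and no outcome for withdrawn patients, so there is no figure of its own to reproduce. The following inputs are assumptions, apart from the target:

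- p: share of an arm withdrawn (10% of 20 patients is 2, 30% is 6).
- G: how much worse withdrawn patients' unobserved change would be than the full-arm mean, 0.5 to 1.0 grade.
- Target difference: 0.5 grade (section 7.2).
- Withdrawn patients contribute no value.

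The observed arm mean is then too favourable by G × p/(1 − p), so the bias in the difference between arms A and B is

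G × [pA/(1 − pA) − pB/(1 − pB)].

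| pA v pB | Bracket | G = 0.5 | G = 1.0 |
|---|---|---|---|
| 10% v 0% | 0.111 − 0 = 0.111 | 0.06 | 0.11 |
| 20% v 5% | 0.250 − 0.053 = 0.197 | 0.10 | 0.20 |
| 30% v 10% | 0.429 − 0.111 = 0.317 | 0.16 | 0.32 |
| 10% v 10% | 0 | 0 | 0 |

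Against the target, the non-zero entries run from 0.056/0.5 = 11% to 0.317/0.5 = 63%.

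If G is measured instead against the retained patients' mean, the bias is G × (pA − pB). That gives 0.05 to 0.10 grade for 10% v 0% and 0.10 to 0.20 for 30% v 10%.

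The bias is zero when G = 0, or when p and G are equal in both arms. It changes sign if withdrawn patients would have done better. The calculation concerns means, whereas the outcome is a median change compared by ranks, so it shows order of magnitude only.

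**The case against.** The best counter-argument is that section 3.5 does not say what patients are withdrawn from, does not end data collection in terms, and discards no earlier scores. The time limit in 4.2.1 may only mark the study window of up to 72 hours. This stands in part: the wording admits that reading. But no passage supports it expressly, and staff following 3.5 and 4.2.1 would have reason to stop grading.

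A reader might infer that an arm with more intolerance will look better on pourability. The documents do not support that. None of the complications anticipated in 6.1 is thicker sputum, and clinician concern under 3.5 need not relate to the device. The direction is unknown.

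A reader might also infer that deaths drop out of the ICU mortality comparison. Section 3.4 (ii) expressly keeps patients without capacity who die, so at least some deaths stay in. What is unclear is whether that rule still applies to someone already withdrawn under 3.5.

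Section 7.1 calls the trial a pilot, not powered for formal comparison. That lowers the consequence, and it would be too strong to say that the randomised comparison is broken. It does not remove the point: tests are planned all the same, and the distributions within each arm can be distorted even without a comparison.

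Finally, section 7.7 refers to a statistical analysis plan that is not shown. Analysis sets and missing-data methods can be left to it. Gradings that were never taken cannot be recovered there.

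**Conclusion.** The point holds as a risk created by the protocol's own data-collection rules. Sections 3.5 and 4.2.1 together end the primary outcome's data at an event that treatment may cause, and the single retention rule in 3.4 (ii) does not cover that event.

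Bias between arms is possible, not certain: it needs withdrawal that is related to outcome and that differs between arms. Distortion of an arm's own distribution needs only the first condition. Neither the direction nor the size can be derived from the documents. The range of about 0.06 to 0.3 grade rests wholly on the assumed withdrawal shares and deficits, and on withdrawn patients contributing nothing. If their earlier scores count, the effect depends instead on how far those scores differ from what the full 72 hours would have shown.

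The change is worth making because it is cheap and the missing gradings cannot be obtained later.

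**What to change.** In section 3.5, leave the clinical grounds for stopping as they are. Add that stopping nebulisation does not by itself end study data collection. Where consent stands and the airway is in place, continue the scheduled 10:00 and 16:00 gradings to 72 hours. Collect ventilator time, ICU stay and ICU mortality for every randomised patient. Say how this fits with the retention rule in 3.4 (ii) and the treatment stop in section 5, so that the three passages agree.

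In section 4.2.1, replace the limit to time on study with the 72-hour study window, and state that patients are summarised in the arm to which they were allocated.

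It would be wrong to go further and limit study withdrawal to withdrawn consent. That would remove the treating clinician's stated ground for withdrawal, which is not a statistical matter.

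The cost is protocol wording and a few gradings. The schedule has two gradings a day over three days, at most six per patient, so fewer remain after a stop. One downside is that scores after stopping may reflect rescue therapy and dilute the on-treatment contrast. An on-treatment sensitivity analysis can show how much.

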## **4 Trial procedures**

### **4.1 Study schedule – Please see study flow chart**

#### **Visit 1: Screening**

- Assess if patient meets the entry criteria
- Give verbal and written information either to patient if they have capacity or legal representative.

#### **Visit 2: Randomisation and undertaking of study**

Patient randomised to Continuous nebulisation of 0.9% normal saline using the Aerogen Solo Nebuliser (50mls) OR Intermittent nebulisation of 0.9% normal saline using the Aerogen Solo Nebuliser (5mls, 6 hourly) OR Intermittent standard nebulisation of 0.9% normal saline using the Intersurgical Cirrus 2 self-sealing Jet Nebuliser (5 mls, 6 hourly)

### **4.2 Study Outcome Measures**

#### **4.2.1 Primary Outcome Measure**

- Median change of all viscosity (pourability) of respiratory secretions as assessed by a dedicated team or physiotherapists using the Qualitative Sputum Assessment Tool Scores taken at 10:00 and 16:00 while the patient is recruited to the study

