### Exclusion Criteria:

Pregnancy  
 Pulmonary embolus  
 Heart Failure (NYHA Grade III/IV)  
 Clinical evidence of frank pulmonary oedema

Initial sample of sputum obtained and Qualitative Sputum Assessment undertaken as follows:

| Volume (mls) |                                                                                                   |                      |  |
|--------------|---------------------------------------------------------------------------------------------------|----------------------|--|
| Type         | M, Muroid (no evidence of pus)                                                                    |                      |  |
|              | P, Purulent (uniformly purulent)
(Colour also recorded)                                        | Predominantly yellow |  |
|              |                                                                                                   | Predominantly green  |  |
|              | MP, Mucopurulent (mixed)
(Divided into 3 grades depending whether pus or mucus is predominant) | MMP                  |  |
|              |                                                                                                   | MP                   |  |
|              |                                                                                                   | MPP                  |  |
| Pourability  | Grade 1 - adheres closely to the container                                                        |                      |  |
|              | Grade ½(1.5)                                                                                      |                      |  |
|              | Grade 2 - moves slowly with gravity                                                               |                      |  |
|              | Grade 2/3(2.5)                                                                                    |                      |  |
|              | Grade 3 – slides in one mass                                                                      |                      |  |
|              | Grade ¾(3.5)                                                                                      |                      |  |
|              | Grade 4 – pours easily but may have viscid particles                                              |                      |  |

Randomisation

10

[figure not shown]

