#### **4.2.2 Secondary Outcome Measure**

- Volume of secretions (increased or decreased may be beneficial)
- Work of breathing
- Airway resistance
- Number of additional nebulised doses of saline or other drugs administered during the study period
- Ease of sampling, in opinion of treating nurse
- Frequency of requiring changing the HME filter
- Length of time on ventilator
- Length of stay in ICU
- ICU Mortality

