### **7.2 Primary efficacy analysis**

A median reduction in the sputum viscosity by 0.5 on a pourability scale for respiratory sections between the three humidification methods tested.

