## **15. FUNDING**

The work has been funded by an unrestricted research grant and equipment from Aerogen Limited.

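### The protocol makes no provision for blinded grading of its subjective primary outcome, although the arms look different and the target difference is one scale step

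*Protocol*

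**What the plan says.** Section 4.2.1 defines the primary outcome as a median change in pourability, "as assessed by a dedicated team or physiotherapists using the Qualitative Sputum Assessment Tool Scores taken at 10:00 and 16:00". The tool is set out in the Study Flow Chart. Each grade describes how sputum behaves in its container, for example "Grade 2 - moves slowly with gravity", with half grades between the whole ones. Section 7.6 works from the same scale, "assuming the score is 1 to 4 in 0.5 increments at each time point", and section 7.2 gives the target: "A median reduction in the sputum viscosity by 0.5 on a pourability scale".

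Section 3.1 lists three arms: a mesh nebuliser run continuously from a syringe feed, the same mesh nebuliser used intermittently, and an intermittent jet nebuliser. Section 1.2 says that the mesh technology may be the better one. Section 15 states: "The work has been funded by an unrestricted research grant and equipment from Aerogen Limited".

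Section 9.1 provides for web-based randomisation. No legible part of the protocol mentions blinding, masking, coded samples or grading away from the bedside. Nor does it call the trial open-label.

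**The concern.** A half-step visual grade leaves room for judgement on borderline samples. Anyone at the bedside can see which device is in use and how it is run. A grader who knows the arm, and has read in the protocol that mesh may be superior, can lean towards the expected answer without meaning to.

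The matter belongs in the protocol because it concerns conduct. Once samples have been graded by someone who knows the arm, no analysis plan can undo it. At stake are the primary comparison and the distributions that section 7.1 wants for planning a later study. A favourable result for the funder's device on an unmasked subjective grade would also be open to challenge.

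**Working it through.** **Inputs**
- Scale 1 to 4 in steps of 0.5; 20 patients per group; 0.0167 per pairwise comparison (section 7.6).
- Target difference 0.5 (section 7.2).
- A grade of 1 to 3 is needed for entry (section 3.2), and the initial sample is graded before randomisation (Study Flow Chart).
- No standard deviation and no size of bias is given, so both are assumed below.

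**1. The plan's own scale.** The number of grades is (4 - 1)/0.5 + 1 = 7. The change runs from 1 - 4 = -3 to 4 - 1 = +3, as section 7.6 says. The target is 0.5/0.5 = 1 step.

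**2. Why the bias need not cancel.** Change is a later grade minus the baseline grade. If baseline is the grade made before randomisation, allocation cannot affect it, whereas every later grade can be affected. The lean then passes whole into the change score. In continuous mesh versus intermittent mesh, an expectation shared by both mesh arms would cancel. In the two jet-versus-mesh comparisons it would not.

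**3. Mean shift, under assumed fractions.** Shift = fraction of mesh readings moved up one step x 0.5.
- One third: 1/3 x 0.5 = 0.17, a third of the target.
- One half: 1/2 x 0.5 = 0.25, half of the target.
- All: 1 x 0.5 = 0.5, the whole target.

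**4. The outcome is a median, which moves in jumps.** Take 20 patients and move 5 of those with no change up one step. The mean shift is 5 x 0.5/20 = 0.125 in both cases below.
- Start with 12 at 0 and 8 at 0.5 (median 0). Afterwards 7 are at 0 and 13 at 0.5, so the median is 0.5: the full target.
- Start with 18 at 0 and 2 at 0.5 (median 0). Afterwards 13 are at 0 and 7 at 0.5, so the median is still 0.

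The same lean in grading can therefore produce the whole target or nothing.

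**5. Chance of a false positive if the devices do not differ.** Section 7.6 treats the change as continuous, so I used a two-sample t test, two-sided at 0.0167, with 20 per group. The noncentrality is (shift/SD) x sqrt(20/2). The Kruskal-Wallis test named in the Synopsis would give somewhat different figures.

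| Assumed shift | SD 0.5 | SD 0.75 | SD 1.0 | SD 1.5 |
|---|---|---|---|---|
| 0.1 | 4% | 3% | 2% | 2% |
| 0.25 | 19% | 8% | 5% | 3% |
| 0.5 | 74% | 36% | 19% | 8% |

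With no shift the rate is 1.67%. The result depends almost wholly on two quantities that the protocol does not give.

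**The case against.** The protocol is silent; it does not say that graders know the arm. Section 4.2.1 names a dedicated team or physiotherapists, and a dedicated team might already work apart from the bedside. Part of the flow chart is not shown in the text available. This stands as far as it goes: a reader might infer that the trial is declared unblinded, but that is an inference from the visible devices. It does not answer the point, because nothing in 4.2.1 keeps the allocation from the grader.

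A reader might also infer that allocation is not concealed. The documents do not support that. Concealment concerns the time before assignment, and randomisation is computer-generated and web-based (Synopsis, section 9.1). The gap is in assessor blinding.

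A reader might take "Ease of sampling, in opinion of treating nurse" in section 4.2.2 to show that nurses collect and physiotherapists grade, so that the roles are already separate. It shows only whose opinion is recorded. The protocol does not say who takes the sample.

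The study is a pilot, and section 7.1 says it lacks the power for formal comparison. That limits the harm. But the Synopsis names a between-group test, section 7.6 lists three pairwise comparisons, and section 17 expects the results to help inform practice.

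The grant is unrestricted and a trials unit analyses the data (section 7.7). Nothing suggests impropriety. Independent analysis does not, however, correct a grade that was biased when it was made.

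**Conclusion.** The point holds in this form: blinded grading of a subjective primary outcome is not provided for, in a setting where the arms are recognisable, the protocol states an expectation in favour of mesh, and the target is one scale step. The bias risk applies to the two jet-versus-mesh comparisons.

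Its size is unknown. The 0.17 and 0.25 shifts are shifts in a mean under assumed fractions, while the outcome is a median. They illustrate scale and are not estimates. To move the mean by the full target, every mesh reading would have to shift one step, although a median can jump a full step with fewer. The conclusion also assumes that the grade made before randomisation serves as baseline. If a grade made after randomisation were used instead, part of a constant lean would cancel.

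This should be changed before samples are graded. It alters no figure stated in the protocol.

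**What to change.** Amend section 4.2.1 so that:
- each 10:00 and 16:00 sample goes into a pot labelled only with a study code and the time;
- the pot is graded away from the bedside by a member of the existing grading team who is not treating that patient and is not told the allocation;
- where this is not possible, the grade is recorded as unblinded.

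State that nurse-rated ease of sampling is an unblinded outcome.

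This reduces the bias but does not remove it: collection of the sample and additional nebulised doses stay in the hands of staff who can see the device.

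The cost is labelling and passing the pot to a colleague. The Schedule of Assessments has two gradings a day for three days, so 2 x 3 = 6 pots per patient and at most 6 x 60 = 360 in all. Interventions, sampling times, endpoint and sample size are unchanged. The protocol does not show that an uninvolved grader is on hand at both times, so this should be confirmed before the amendment is made.
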